**Ethics and dissemination:**

Ethics approval was not required for this study. This project has been approved by the CPRD's Independent Scientific Advisory Committee (ISAC). We will disseminate our findings via publications in international peer-reviewed journals and presentations at international conferences.

Strengths and limitations of this study
We will use data from a large sample of patients prescribed smoking cessation treatment in UK general practices. This means we will have substantial power to detect even relatively small effects, or effects on rare outcomes.We will use three statistical approaches to overcome confounding. These approaches depend on distinct assumptions. Triangulating across different methods will help provide more robust evidence about the effects of these medications.Our study will use observational data and so results can suffer from unobserved confounding. We will report in detail the confounding structure, and detail the methods we used to overcome this limitation.The outcomes used in this study will be defined using diagnoses and interactions that occur as part of the patients’ routine care. Different general practices may use a range of Read codes to record diagnoses. We will mitigate this limitation by using validated code lists, where available, to ensure the algorithms we use accurately capture the diagnoses and events of interest.

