### Power calculations

The following power calculations are based on effect sizes and CIs observed in our previously published results, which used data from 110 000 individuals prescribed either varenicline or nicotine replacement therapy.^13^ Based on the rate of 18 000 new prescriptions per year observed in the CPRD from 2006 to 2011,^13^ we estimate that with a further 4 years of follow-up the number of patients prescribed either varenicline or nicotine replacement therapy will have increased by 72 000. Therefore the total expected sample size for analysis will be around 180 000.

In our previous analysis using CPRD data the age-adjusted and sex-adjusted HR for self-harm/suicide for varenicline versus nicotine replacement therapy at 9 months was 0.73 (95% CI 0.54 to 0.99); after adjusting for possible confounders this became 0.90 (95% CI: 0.66 to 1.22).^13^ A 70% increase in sample size would lead to a reduction of the SE by a factor of 1.3, reducing the breadth of the above CI in the adjusted analysis from 0.56 to 0.43.

Rare outcomes, such as self-harm and suicide were used in previous analyses; in this project we will have greater power to explore more common outcome measures. For example, in the previous analysis the 9-month age-adjusted and sex-adjusted HR for all-cause mortality 9 months after first prescription for varenicline versus nicotine replacement therapy was 0.43 (95% CI 0.35 to 0.53); after controlling for possible confounders this became 0.49 (95% CI 0.40 to 0.61). A 70% increase in sample size would lead to a reduction of the SE by a factor of 1.3, reducing the breadth of the above CI in the adjusted analysis from 0.21 to 0.16.

For the effects of varenicline versus nicotine replacement therapy on all-cause mortality, instrumental variable analysis found a risk difference of 0.7 (95% CI −3.3 to 4.7) per 1000 patients treated after 9 months. We estimate that a 70% increase in sample size would narrow the CIs from 8.0 to 6.2.

Using data from our previous project, within 2 years of first prescription, we found 2517 admissions for respiratory disease among 1374 patients; 3144 admissions for cardiovascular disease among 1022 patients; and 3277 admissions for depression or anxiety among 213 patients. This is more events than we found for suicide and self-harm in our previous study; therefore we believe that there will be enough events for this analysis.

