### Statistical analysis

For investigating the effects of varenicline use on each outcome (long-term smoking cessation, frequency of GP and hospital attendance, all-cause and cause-specific mortality, primary care diagnosis of respiratory illness, myocardial infarction, depression or anxiety), we will report a conventional multivariable-adjusted Cox regression, propensity score regression and instrumental variable analysis.

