#### Analysis 1: Conventional cox regression

In our first analysis, a conventional observational analysis, we will estimate HRs of the outcomes using Cox-proportional hazards models and the actual prescriptions issued to the patients.^29^ Each patient's date of entry into the cohort will be the date they were first prescribed a smoking cessation therapy. The date of exit for each outcome will be the date on which they first have an event, or are censored due to end of follow-up or death or leaving the practice. We will report these associations adjusted for basic confounders (age and gender), and results adjusted for all measured covariates described above.

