#### Analysis 2: Propensity score regression

In our second analysis we will construct a sample of patients balanced on covariates and risk factors using a propensity score.^30–33^ We will construct propensity scores using a logistic regression of the actual treatment received on the covariates described above. Therefore, each participant's propensity score will be their conditional probability (odds) of receiving varenicline versus nicotine replacement therapy. We will match each patient receiving varenicline to another patient receiving nicotine replacement therapy with the closest propensity score on a ratio of 1:1 using a nearest neighbour algorithm with no replacement, and matching will be restricted to the common support region. Patients outside the common support region are those prescribed varenicline with propensity scores higher than any patient prescribed nicotine replacement therapy and vice-versa. We will estimate HRs of the outcomes using the propensity score matched sample using Cox regressions using the same entry and exit information as the conventional Cox regression analysis described above.

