#### Analysis 3: Instrumental variable analysis

In our third analysis, we will estimate the effects of smoking cessation therapies on the outcomes using physicians’ prescribing preferences as instruments for the prescriptions the GPs issue to their patients. We cannot directly measure the physicians’ preferences; therefore, we will use the prescriptions they issued to their previous patients as a proxy for their preferences. For example, if the instrument was based on just one previous prescription, physicians who previously prescribed varenicline would be categorised as a varenicline prescriber. As with our previous studies we will use seven prior prescriptions to improve the strength of the instruments.^13^
^34^
^35^ Using multiple prior prescriptions will maximise power. We will report risk differences in the outcomes using additive structural mean models estimated via the generalised method of moments.^36–38^

We will categorise each of the adverse event outcomes as occurring within 3, 6, 9, 12, 24 and 48 months of first prescription. We will do this because methods for conducting survival analysis using instrumental variables are not well developed. We will use Stata 13.1 SE to generate all results. The instrumental variable analysis will be conducted using the ivreg2 command and psmatch2 will be used to construct the propensity score.^31^
^39^
^40^ All SEs will be estimated using cluster robust SEs, which account for clustering of patients within practices.

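### Two analyses report hazard ratios and the instrumental variable analysis reports risk differences, so the planned outputs do not allow a direct comparison of effect size

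*Protocol article*

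**What the plan says.** The Statistical analysis section applies all three methods to every outcome: "we will report a conventional multivariable-adjusted Cox regression, propensity score regression and instrumental variable analysis". The effect measure of each is then fixed in its own subsection of the Protocol article:

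- Analysis 1 (conventional Cox regression): "we will estimate HRs of the outcomes using Cox-proportional hazards models and the actual prescriptions issued to the patients".
- Analysis 2 (propensity score regression): "We will estimate HRs of the outcomes using the propensity score matched sample using Cox regressions".
- Analysis 3 (instrumental variable analysis): "We will report risk differences in the outcomes using additive structural mean models estimated via the generalised method of moments".

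For Analysis 3 the outcomes are made binary: "We will categorise each of the adverse event outcomes as occurring within 3, 6, 9, 12, 24 and 48 months of first prescription". The reason given is that "methods for conducting survival analysis using instrumental variables are not well developed".

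The strengths and limitations list after the abstract gives the purpose of using three methods: "Triangulating across different methods will help provide more robust evidence about the effects of these medications". The same list names unobserved confounding as a limitation of the observational data.

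The article does not say that Analyses 1 and 2 will also produce risk differences, that HRs will be converted, or that the difference between methods will be estimated.

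**The concern.** Analyses 1 and 2 draw on the same measured covariates, so agreement between them says little about confounders that were not measured. Only the IV analysis, which rests on prescriber preference, can speak to those. The informative contrast is therefore adjusted against IV, and that is the pair reported on different scales.

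An HR is relative and a risk difference is absolute. Linking them requires the risk in the NRT group at the same time point. Suppose a reader sees a clearly protective HR beside an IV risk difference near zero with a wide interval. The IV result may contradict the HR, or it may be an imprecise estimate of the same effect. The planned outputs do not separate these two readings. The article intends its findings to go to two medicines regulators, so the distinction matters.

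**Working it through.** **Inputs** (Power calculations section, all-cause mortality at 9 months, varenicline versus NRT, previous study of 110 000 patients)

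- Age- and sex-adjusted HR 0.43 (95% CI 0.35 to 0.53)
- Fully adjusted HR 0.49 (95% CI 0.40 to 0.61)
- On the other scale, "instrumental variable analysis found a risk difference of 0.7" per 1000, 95% CI −3.3 to 4.7
- Risk on NRT, p0: not given, so it is varied below

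**The plan's own figures reproduce.** The HR interval width is 0.61 − 0.40 = 0.21, and 0.21/1.3 = 0.16 as stated. The IV width is 4.7 − (−3.3) = 8.0, and 8.0/1.3 = 6.15, against 6.2 stated. Each width is projected on its own scale and the two are never linked.

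**Placing the HR on the IV scale.** RD = [1 − (1 − p0)^HR] − p0, which for rare events is close to p0 × (HR − 1).

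| Assumed p0 per 1000 | RD per 1000 at HR 0.49 | RD at HR 0.40 | RD at HR 0.61 |
|---|---|---|---|
| 5 | −2.5 | −3.0 | −1.9 |
| 7 | −3.6 | −4.2 | −2.7 |
| 10 | −5.1 | −6.0 | −3.9 |

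The same HR thus implies an absolute effect that doubles over this range, against a fixed IV estimate of 0.7 (−3.3 to 4.7).

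**Indicative test of the difference.** This treats p0 as known and ignores the covariance between estimates that share patients.

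- SE of the IV estimate: 8.0/3.92 = 2.04 per 1000.
- SE of log HR: ln(0.61/0.40)/3.92 = 0.108.
- SE of the converted RD: about p0 × 0.49 × 0.108.
- z = (0.7 + 0.51 × p0)/√(2.04² + SE(RD)²).
- At p0 = 5: z = (0.7 + 2.55)/√(2.04² + 0.26²) = 1.58, p = 0.11.
- At p0 = 10: z = (0.7 + 5.1)/√(2.04² + 0.53²) = 2.75, p = 0.006.
- Intermediate values move gradually: p = 0.07 at 6 per 1000 and 0.04 at 7 per 1000.

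**Is that range of p0 plausible?** A rough value can be backed out from the age- and sex-adjusted HR using var(log HR) = 1/d1 + 1/d0, where d1 and d0 are deaths on varenicline and NRT. Here SE = ln(0.53/0.35)/3.92 = 0.106. With varenicline share a, d1/d0 is about 0.43a/(1 − a). The share is an assumption.

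- a = 50%: d0 ≈ 297 among 55 000, p0 ≈ 5.4 per 1000.
- a = 20%: d0 ≈ 919 among 88 000, p0 ≈ 10.4 per 1000.

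The plausible range therefore covers values at which the two estimates look compatible and values at which they do not.

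**The case against.** Several points on the other side stand.

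- A reader might infer that the methods cannot be compared at all. The article does not support that. In the previous mortality results the HR lies below 1 and excludes it, while the IV point estimate lies slightly above 0 with an interval that includes 0. That can be read without any conversion.
- The study will observe the NRT risk in its own cohort. Its absence from a power section does not mean that the results will omit it, so HRs could be converted afterwards.
- A reader might infer that the time horizons differ as well. This is doubtful. The sections on Outcomes 2 and 4 define windows from 3 to 48 months generally, and the power section quotes 9-month HRs beside a 9-month IV result.
- A reader might infer that the IV analysis uses fewer patients because the instrument needs seven prior prescriptions. The article does not say how patients without seven are handled.
- Whether one method's point estimate falls inside the other's interval is not a valid test of agreement, and the illustration should not be read that way.

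Two objections carry less weight. The stated reason for the IV scale explains why Analysis 3 gives no HR, but not why Analyses 1 and 2 give no risk difference. It can also be said that supplementary estimates belong in a fuller document, and the article does refer to a separate study protocol that is not shown. That document may add a common scale. But the article itself fixes the effect measure of each method, and fixes measures that do not match.

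**Conclusion.** The point holds in a limited form. As fixed in the article, the outputs allow comparison of direction and of compatibility with no effect. They do not allow a direct comparison of effect size between the adjusted and IV estimates, which is the comparison that bears on unmeasured confounding.

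In the mortality example, HR 0.49 stands for anything from about −2.5 to −5.1 per 1000 as the NRT risk goes from 5 to 10 per 1000, and the indicative p value for its difference from the IV estimate goes from 0.11 to 0.006. These figures rest on assumed NRT risks, an assumed varenicline share for the back-calculation, and independence of the two estimates. They show how much depends on the missing link, and do not establish that the previous results disagreed.

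This is a cheap improvement to the plan. It does not make any of the three analyses invalid.

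**What to change.** Keep the HRs from Analyses 1 and 2. For each binary outcome and each window from 3 to 48 months, add:

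1. a covariate-adjusted risk difference, for example from a linear-probability regression on the Analysis 1 covariates, with practice-clustered standard errors, in the same patients as the IV analysis;
2. the risk difference in the propensity-matched sample, with practice-clustered standard errors;
3. the adjusted-minus-IV difference, with a cluster-robust endogeneity test or a practice-level bootstrap interval. The endogeneity test presumes the same covariates in both models. If they differ, use the bootstrap.

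State that this difference is the quantity on which agreement between methods will be judged.

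The cost is extra regressions on outcomes and software already planned. There are two limits. Windowed binary outcomes need a rule for patients who leave the practice before the window closes. Cox regression censors them, whereas the IV analysis already needs such a rule, so the same one should be used. And a common scale does not give the methods a common target effect, so a difference may reflect different target effects and not confounding alone. The report should say so.

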### Socioeconomic variation in effectiveness of smoking cessation treatments

This project will use the entire sample of patients indicated as a smoker at any point after 1 September 2006. We will assign a measure of area level deprivation to each patient using their home address postcode and to each GP using the GP postcode. Deprivation levels will be based on the Indices of Multiple Deprivation (IMD), which are available from the ONS and are updated every 2 years. We will use the most recent IMD statistics preceding the date of entry into the study for each patient. Although area level deprivation statistics will only be a proxy for individual level deprivation, these demonstrate the expected associations with smoking prevalence.^41^ We will investigate whether the proportion of smokers who attend their GP for smoking cessation treatment differs by IMD, and whether there are any differences in prescribing of varenicline versus nicotine replacement products between areas of high and low deprivation.

By using individual and GP level IMD codes, we will investigate whether the effects of smoking cessation therapies differ by IMD at the level of GPs and at the individual level. We will investigate treatment compliance by reporting the total number of prescriptions issued after the initial prescription. We will estimate the effects of smoking cessation therapies within subgroups defined by IMD level at the individual and GP level using the three methods described above, multivariable-adjusted Cox regression, propensity score regression and instrumental variable analysis.^29^
^32^
^42^ The cohort of patients will be defined as described above. We will report these associations adjusted for basic confounders (age and gender), and results adjusted for all measured covariates described above. Analyses will account for clustering of patients by GPs.

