To investigate differences in healthcare-seeking behaviour of smokers by SEP we will combine the sample used for the health outcomes described above with a sample of all other patients indicated as a current smoker after the 1 September 2006.

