##### Follow-up

Follow-up will end with the earliest of either an ‘event’ or censoring due to the end of registration or death.

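### The comparison of treatment uptake by deprivation has no time base, so differences in time observed as a registered smoker could pass for differences in uptake

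*Protocol article*

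**What the plan says.** The population is given twice. The section on socioeconomic variation in effectiveness states: "This project will use the entire sample of patients indicated as a smoker at any point after 1 September 2006". The end of the power section describes the same group as the treated cohort combined with "a sample of all other patients indicated as a current smoker after the 1 September 2006", and gives healthcare-seeking by socioeconomic position as the purpose.

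The socioeconomic section then sets two descriptive comparisons. The first is uptake: "We will investigate whether the proportion of smokers who attend their GP for smoking cessation treatment differs by IMD". The second is product choice: "whether there are any differences in prescribing of varenicline versus nicotine replacement products between areas of high and low deprivation". This point concerns the first.

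The only defined start of follow-up is in Analysis 1: "Each patient's date of entry into the cohort will be the date they were first prescribed a smoking cessation therapy". Patients leave when they have an event or "are censored due to end of follow-up or death or leaving the practice". The three named methods (Cox, propensity score, instrumental variable) are assigned to a different question: "We will estimate the effects of smoking cessation therapies within subgroups defined by IMD level at the individual and GP level using the three methods".

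**The concern.** The denominator is open-ended and the measure is a simple proportion. One smoker may contribute many years in which a first prescription could be recorded. Another may contribute only months, having been recorded as a smoker late, moved practice or died. A proportion counts both equally.

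If observed time differs by deprivation, the comparison mixes two things: how readily smokers seek treatment, and how long they could be seen doing so. Adjusting for age, gender or other covariates, or allowing for clustering, does not equalise observation time.

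The result will be read as evidence on inequality in access. The study aims cite earlier primary care data in which more deprived smokers were more likely to receive interventions. A measure that mixes uptake with observation time could neither confirm nor contradict that cleanly.

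**Working it through.** **1. The plan's own figures.** No sample size, treatment rate or observation time is given for the uptake comparison. The stated total of about 180 000 counts treated patients only: 110 000 + 4 × 18 000 = 182 000, which agrees. It does not bear on this point.

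**2. Can the defined clock be used?** No. Entry under Analysis 1 is the first prescription, which a never-treated smoker does not have. The socioeconomic section also assigns IMD from the latest statistics before each patient's study entry, so it needs an entry date for untreated smokers that is not defined anywhere.

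**3. Do numerator and denominator share eligibility?** Not as written. The inclusion criteria exclude patients registered for under 365 days before their first prescription. The added group of all other current smokers is described without that rule. Read literally, a recently registered smoker can count in the denominator but could not yet count in the numerator.

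**4. How large could the artefact be?** Assumptions, none from the document: a constant first-treatment rate h, the same in both IMD groups, and everyone in a group observed for T years as a registered smoker. Then

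proportion treated = 1 − exp(−h × T).

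The true rate ratio is 1.00 in every row.

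| h per year | T, group A v B (years) | Proportion treated, A v B | Difference (points) |
|---|---|---|---|
| 0.05 | 5 v 5 | 22.1% v 22.1% | 0 |
| 0.05 | 5 v 4.5 | 22.1% v 20.1% | 2.0 |
| 0.05 | 5 v 4 | 22.1% v 18.1% | 4.0 |
| 0.05 | 6 v 4 | 25.9% v 18.1% | 7.8 |
| 0.03 | 5 v 4 | 13.9% v 11.3% | 2.6 |
| 0.10 | 5 v 4 | 39.35% v 32.97% | 6.4 |

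Worked row: 1 − exp(−0.05 × 5) = 1 − exp(−0.25) = 0.221, and 1 − exp(−0.05 × 4) = 1 − exp(−0.20) = 0.181. The ratio B/A is 0.181/0.221 = 0.82. Either deprivation group could be A.

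**5. The same groups with a time base.** The rate per smoker-year is 0.05 in both, a ratio of 1.00. The 12-month cumulative incidence is 1 − exp(−0.05) = 4.9% in both. Under these assumptions the artefact disappears whatever the observation time.

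**The case against.** The strongest reply is that this is a condensed article. It never uses the words ever treated and states no numerator window. The full protocol approved by the CPRD's scientific advisory committee is not shown and may supply one. A reader might infer that the plan has deliberately chosen an ever-treated proportion. That is the natural reading of an open-ended denominator with an unwindowed proportion, but it is an inference. What remains is that the article fixes the population and the type of measure. It also states a time base for its other analyses: windows of 3 to 48 months, and follow-up defined by "Follow-up will end with the earliest of either an ‘event’ or censoring due to the end of registration or death". This comparison has none.

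A reader might also infer that unequal observation time will produce a false deprivation gradient. The document does not support that. It gives no smoker-time by IMD. Shorter registration in deprived groups would lower their proportion, while earlier quitting in less deprived groups would lower theirs, so the two could offset. With equal time the artefact is zero. This objection stands, and the point is therefore conditional.

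Finally, the uptake comparison is descriptive and secondary to the question of whether treatment effects differ by deprivation. That is fair. The effect analyses start at first prescription and use censoring or fixed windows, so they are untouched.

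**Conclusion.** The concern holds in a conditional form. As written, the uptake comparison uses a plain proportion of an open-ended smoker population, with no index date for untreated smokers and no time base. Differences between IMD groups in observed smoker-time could therefore appear as differences in uptake, and nothing stated would separate the two.

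The size and direction are unknown. The illustrative 4.0-point gap (22.1% v 18.1%) rests wholly on an assumed rate of 5% per year and an assumed 5 v 4 years of observation. It shows that a bias is possible, not that one exists. The varenicline v NRT effect estimates, including those within IMD subgroups, are not affected. The change should be made because it is cheap and settles the measure before results are seen.

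**What to change.** - **Index date.** For every smoker, use the first current-smoker record on or after 1 September 2006 that meets the same prior-registration rule as the treated cohort, so that numerator and denominator share eligibility. This also supplies the entry date needed to assign IMD.
- **Measure.** Replace the plain proportion with time to, or rate of, first varenicline or NRT prescription. Censor at end of registration, death or end of data. Compare IMD groups with standard errors clustered by practice.
- **Fixed window, if wanted.** Report a figure such as 12-month uptake as a cumulative incidence with censoring. Do not restrict to patients who stay registered for 12 months, because that selects on later survival and on not moving.
- **Sensitivity analysis.** Censor at an ex-smoker record only as a sensitivity analysis. The outcome section says status cannot be determined for patients who do not return, and that 74% of treated patients had a later smoking record, so recorded quitting depends on attendance.

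The cost is about a paragraph of text, slightly more programming, and a summary less simple than a raw proportion. The prescription, smoking-status, registration and death data are ones the study already relies on.
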